## Abstract

Ideally, patient-centered trial information material encourages the discussion with the treating physician, and helps patients making trade-offs regarding treatment decisions In a situation of possible equivalent treatment options in terms of overall survival (OS), it can make it easier to weigh up advantages and disadvantages. Preferences for choice of treatment in esophageal cancer (EC) are complex, and no standardized assessment tools are available. We will explore patient’s factors for treatment choice and develop a comprehensive patient information leaflet for the inclusion into randomized controlled trials (RCT) on EC. We conduct a cross-sectional, observational study based on a mixed-methods design with patients suffering from non-metastatic EC with post-neoadjuvant complete response after neoadjuvant chemotherapy (nCT) or neoadjuvant chemoradiation (nCRT), to develop patient-centered trial information material. This pilot study is performed in a concept development phase and a subsequent pilot phase. We start with patient interviews (*n* = 10–15) in the concept development phase to evaluate patients’ needs, and develop a Preference and Decision Aid Questionnaire (PDAQ). We pre-test the PDAQ with another *n* = 10 patients with EC after nCT or nCRT, former patients from a self-help organization, and *n* = 10 medical experts for their comments on the questionnaire. In the pilot phase, a multicenter trial using the PDAQ and additional measures is carried out (*n* = 120). Based on evidence of a possible equivalence in terms of OS of the treatment options “surgery as needed” and “surgery on principle” in patients with post-neoadjuvant complete response of EC, this pilot study on patient participation is conducted to assess patient’s needs and preferences, and optimize patients’ inclusion in a planned RCT. The aim is to develop patient-centered trial information material for the RCT to increase patients’ consent and compliance with the randomized treatment. The trial is registered at the German Clinical Trials Register (DRKS00022050, October 15, 2020).

## Introduction

Patient-centered health care considers patients and professionals as partners and has its focus on the individual patient’s treatment preferences and needs. Thus, patients should be treated as partners with solidarity, empathy, and collaboration, but also with responsibilities (1). An essential point of a modern high-quality health care system is the treatment decision-making process, in which the patient is actively involved by getting relevant information in terms of treatment options. Treatment decision for patients with cancer is a complex task and requires a patient-oriented information process. In the process of providing information, it has to be considered that the patient is in a highly distressed situation in consequence of the diagnosis. Balancing of risks and benefits aimed to reach an understanding of the patient in a difficult situation of treatment options is an important challenge in the process of informed consent in clinical trials. This is regarded as essential also for the information process in randomized trials, and it is anticipated that it will improve the recruitment process and consent to randomization (2). Ideally, patient-centered trial information material encourages the discussion with the treating physician, and helps patients making trade-offs that reflect their own values and preferences (3). In consequence, patient-centered trial information material should include evidence-based information on disease and treatment options, postoperative mortality and morbidity, intermediate and long-term outcomes, side-effects, and burdens to daily life of respective treatment options (4). Educational material should be included, addressing risks and benefits of treatment options. The ethically optimal procedure is one that empowers patients to make preference-sensitive decisions consistent with their goals, values, and preferences (5). Even though shared decision making is not the envisaged process in randomized trials, value clarification is important. The decision to take part in a randomized clinical trial is driven by subjective and intuitive behavior [e.g., feeling of discomfort and vulnerability (2, 5, 6)] and has also psychological, social, and emotional factors (7). The tools of shared decision making processes are useful to gain a more comprehensive understanding of patients’ attitudes towards treatment and clinical trials in general, and to take this information into account in the study information material.

The standard of care for patients with non-metastatic esophageal cancer (EC) after neoadjuvant chemoradiotherapy (nCRT) or neoadjuvant chemotherapy (nCT) is principal surgery, 4–8 weeks after nCRT/nCT (8–10). Evaluations of health-related quality of life (HRQoL) for patients who had EC treated with nCRT showed detrimental effects in physical functioning, odynophagia, fatigue, weight loss, and global quality of life in those 4–6 weeks prior to surgery (11). Rapidly physical functioning, odynophagia, and sensory symptoms were restored to pretreatment levels respectively 4–10 weeks after nCRT (11). After surgery role and social function, fatigue, diarrhoea, appetite loss, nausea and vomiting became substantially worse compared to a reference population. Overall HRQL in long-term survivors after esophagectomy did not improve between 6 months and 3 years after surgery, and was worse than that in a comparable reference population (12).

Another as equivalent hypothesized treatment option following nCRT or nCT in terms of overall patient survival is close surveillance with surgery only as needed in persisting or recurring loco-regional tumor (13). A survival disadvantage of delayed surgery in case of local tumor relapse appears unlikely in a protocol of close surveillance of clinical complete response (cCR) (10, 14). Moreover, HRQoL can be restored to levels before treatment after 4–10 weeks after completion of nCRT (11). In a comparative analysis, 36 patients who underwent nCRT and surveillance were matched to 36 patients who underwent nCRT followed by direct surgery. Estimated median overall survival (OS) was equivalent in the surveillance group than in the standard surgery group (58 months, vs. 51 months, *p* = .28). All patients in the surveillance group with loco-regional recurrence in the absence of distant metastases underwent surgery as needed with excellent outcome (median OS 58 months). Moreover, distant metastasis rate was comparable in both groups (active surveillance: 31% vs. standard surgery: 28%) (10). Additionally, we conducted a systematic scoping review of all available studies on the comparison of “surgery as needed” versus “surgery on principle” (15). The results suggest that both post-neoadjuvant treatments are feasible to evaluate in a prospective and comparative clinical trial for complete clinical responders without compromising on OS. Thus, post-neoadjuvant identification of patients with pathological complete response (pCR) followed by closed-meshed surveillance and surgery as needed in case of local tumor recurrence might be a treatment alternative to surgery on principle for patients with post-neoadjuvant pCR. Before practice in routine clinical pathways this has to be evaluated by prospective randomized controlled trials (RCTs). Quality of life is expected to be clearly improved in this group of patients. Omission of esophagectomy reduces length of therapy, complication rate, and time of hospital stay resulting in a reduced treatment cost and faster return to socioeconomic productive work life of the patients.

Clinical response evaluation in the subsequent RCT comprises esophagogastroscopy to locate mucosal tumor, residual or scarred lesions, endoscopic deep biopsies of tumor area to obtain proof or exclusion of residual tumor, endoscopic ultrasound plus fine needle aspiration (FNA) of suspicious lymph nodes to proof or exclude of residual tumor, pathology workup of biopsies and FNA aspirates and F18-FDG-PET CT (whole body) for radiographic/metabolic targeting of loco-regional/distant disease. Clinical response evaluation is done 4-8 weeks after completion of neoadjuvant treatment. In case of clinical histology-proven positive tumor status and/or loco-regional metabolic positive lymph nodes without distant metastasis after clinical response evaluation (“non-CR”), treatment is surgery (Esophagectomy). Patients without histologic evidence of local residual disease, without loco-regional metabolic positive lymph nodes and without evidence for distant metastasis will be considered to be clinically complete responders (“clinical CR”) and will be to directly proceed with consecutive close-meshed surveillance visits with surgery only in the event of a local tumor recurrence. 

In the situation of possible equivalent treatment options in terms of OS, patient-centered trial information can make it easier to weigh up the advantages and disadvantages of the alternatives. This understanding is the prerequisite for an informed decision. Treatment options can be described by discrete attributes, and the value of the treatment options depends on the nature and level of these attributes. A prospective study showed that 5-year OS, long-term HRQoL, and the chance that esophagectomy is still necessary influenced patients’ preference for either active surveillance or planned surgery after nCRT for esophageal cancer (16). A study among patients who had undergone esophagectomy concluded that patients are willing to trade-off 16% of their 5-year survival chance to achieve an improvement in early outcomes (17). Using regression coefficients (β) as measures for the relative importance of attributes, a patient survey assessing preferences of patients towards surgery for preoperative esophagogastric cancer evaluated that patients preferred a better quality of life (QoL) (β = 1.19), higher cure rate (β = 0.82), and lower morbidity (β = 0.70) over treatment in a specialist hospital (β = 0.26) (4).

The factors influencing patients’ treatment preferences for choice of treatment in esophageal cancer are complex, and no standardized assessment tools are available.

### Aims and Purpose of the Study

The purpose of the study is to develop patient-centered trial information material to be used in the planned RCT designed to compare the treatment regimens “surgery as needed” and “surgery on principle” in patients with post-neoadjuvant complete response of EC with respect to OS. The aim of this study is to improve the recruitment of patients in the planned RCT and to improve their consent to randomization and their adherence to the randomized treatment. In a first step we will assess patients’ information needs and values in terms of the two treatment options of the envisaged RCT by qualitative interviews. Based on these results a Preference and Decision Aid Questionnaire (PDAQ) will be designed in the first part of the project (i.e., development phase). After pre-testing this questionnaire will be used in a survey in the second part of the project (i.e., pilot testing phase) for the evaluation of patients’ preferences and analysis of associations with fear of progression, depression, anxiety, health-related quality of life and disease related social support.

Further, the pilot phase will provide information on the likelihood of patients consenting to participation in the RCT, accepting randomization, and about their compliance with treatment allocation. Hereby we intend to improve the inclusion rate and to optimize the estimations on patient refusal rate, drop-out rate, and cross-over-rate of the envisaged RCT.

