## Methods

In a cross-sectional, observational study we are assessing patients’ needs and preferences towards the treatment options of the planned RCT “Surgery as needed versus surgery on principle in patients with post-neoadjuvant complete tumor response of esophageal cancer (ESORES)” in two consecutive phases: (1) A development phase and (2) a pilot testing phase.

We start with detailed qualitative patient interviews (*n* = 10–15) in the development phase. Patients who had already undergone nCT or nCRT for EC and partially also surgery are asked for their needs, preferences, and attitudes towards choice of treatment. Particularly, patients are asked regarding their potential willingness to participate, to accept randomization, and to comply with the treatment to which they will be allocated.

Additionally, *n* = 10 medical experts in the field of EC treatment (i.e., 3–5 clinicians out of the field of EC treatment, 3–5 nurses, and psycho-oncologists) are asked regarding their experiences with patients in terms of patients’ attitudes towards treatment choices, preferred treatment option, and the reasons for it.

With respect to patient participation, *n* = 2 members of an adequate Peer-Support Organization (18) are asked to review the interview guidelines, the interview statements, and the provisional PDAQ, and to give comments on them.

Based on the information regarding patients’ goals and attitudes, peer-support group members and medical experts’ attitudes, the final PDAQ will be constructed. In the subsequent pilot phase, *n* = 120 patients with EC after nCT or nCRT are asked to fill in the PDAQ in a multicenter trial in order to develop patient-centered trial information to serve as study material in the envisaged RCT. The specific study phases are depicted in **Table 1**. Furthermore, details about the study procedures of the pilot phase are provided in **Figure 1**.

**Table 1 T1:** Study procedures.

Phase	Study Procedures
**Development phase (0–7 months)**	Interview guideline
	Patient eligibility
	Enrollment, study information, and informed consent
	Disease specific treatment data of study condition (EC)
	Interviews
	Patients in individual interviews (*n* = 10–15)
	Medical experts (*n* = 10)
	PDAQ
	Development
	Pre-testing (*n* = 10 patients; *n* = 2 patients advocates)
	Adaption
**Pilot phase (8–20 months)**	PDAQ Survey (*n* = 120 patients including)
	Age
	Gender
	Education
	FoP-Q-SF
	PHQ-9
	GAD-7
	EORTC-QoL-C30
	OES18

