### Participants

In the development phase patients’ screening for trial eligibility will be performed at the Medical Center University Freiburg. In the pilot phase the PDAQ survey will be performed multicentric in total five specialized centers in Germany. Eligible patients according to the inclusion criteria will be identified through medical records and will be patients after neoadjuvant treatment and before or after surgery. Patients, who participated in the pilot phase, will not participate in the consecutive RCT.

Patient participation in the study is voluntary and patients can withdraw their consent to participate at any time during the study without incurring disadvantages in treatment. Patients will be given sufficient time to read and understand the study information, to review the information, ask questions, and receive satisfactory answers from the trial physician. Subsequently, patients will be asked to sign the informed consent after completed information process. Patients eligible to participate in the study (development phase and pilot phase) have to fulfill the following inclusion criteria:

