#### Pilot Phase

The pilot phase mainly has two objectives:

1) The development of patient-centered information material optimally fulfilling the individual needs of the patients with the aim to improve the recruitment of patients for the clinical trial and to improve their consent to randomization between the standard treatment “surgery on principle” and the experimental treatment “surveillance and surgery as needed” and their adherence to the randomized treatment.

2) To verify assumptions for sample size calculation for the planned RCT regarding the rate of EAC vs. ESCC, the rate of nCRT vs. nCT, and the pCR rate after surgery.

With regard to objective 1) the effects of socio-demographic, disease-specific, and psycho-social factors on patients’ treatment preference (“surgery on principle” versus “surveillance and surgery as needed”) will be analyzed. Additionally to descriptive analyses, univariate and multivariate logistic regression models will be used to identify which factors may be associated with patients’ treatment preference. Effect sizes will be quantified by odds ratios with 95%-confidence intervals and tested using the Wald test. P-values will be interpreted in a descriptive sense. Those factors identified as influential with a relevant effect size will then especially be considered in the development of the patient-centered trial information material and check-list for clinicians in the planned RCT.

Sample size was chosen based on feasibility without formal sample size planning based on statistical power calculations. The inclusion of 120 patients from 5 clinical centers within a time period of 6 to 12 months was regarded as feasible. The following statistical consideration only exemplifies the possible conclusions with the chosen sample size: 120 patients would provide 80% power for an identification of a factor influencing patients’ preference with an odds ratio of 3 at a significance level of.05, considering adjustment for other correlated factors (variance inflation factor 1.2). With regard to objective 2) descriptive analyses of tumor type, type of neoadjuvant therapy, and of pCR status after surgery will be performed.

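### The aim of refining the RCT's refusal, drop-out and cross-over estimates has no matching analysis in the pilot, and a one-time survey cannot give a drop-out rate

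*Protocol article*

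**What the plan says.** Under Aims and Purpose of the Study, the article states that "the pilot phase will provide information on the likelihood of patients consenting to participation in the RCT, accepting randomization" and compliance with the allocated treatment. The purpose given is to "optimize the estimations on patient refusal rate, drop-out rate, and cross-over-rate of the envisaged RCT".

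The Pilot Phase part of Biostatistical Planning and Analysis names two main objectives. The first is information material that improves recruitment, consent to randomization and adherence. For it, besides descriptive analyses, "univariate and multivariate logistic regression models will be used to identify which factors may be associated with" patients' preference for one arm or the other. The second is to check assumptions behind the RCT's sample size: the split of EAC and ESCC, the split of nCRT and nCT, and the pCR rate. All three are to be described only.

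In Methods, within the account of the 10–15 development-phase interviews, "patients are asked regarding their potential willingness to participate, to accept randomization, and to comply with the treatment" they would be allocated to. The interview guide under Study Procedures closes with a question on accepting assignment to one named group or asking to change. The final PDAQ for the survey is described as covering needs, preferences and what influences them.

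On design, Methods says "In a cross-sectional, observational study we are assessing" needs and preferences. Participants adds that those enrolled "will be patients after neoadjuvant treatment and before or after surgery", and that "Patients, who participated in the pilot phase, will not participate in the consecutive RCT".

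**The concern.** The aim and the analysis do not meet. The RCT planners are told to expect better estimates of three quantities, yet the section that fixes the analysis neither uses any of them as an outcome nor lists them among the assumptions to verify. Arm preference does not stand in for them: a factor that predicts which arm a patient prefers need not predict whether the patient would refuse randomization or leave an unwanted arm.

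Two things are at stake. First, refusal and cross-over affect the RCT's recruitment and power, and the Discussion reports that compliance in earlier trials differed sharply between arms and was worse in the surgical arms. It presents this pilot as part of the answer. Second, the biostatistics section says that factors found in the preference model will receive special weight in the information material. That material is supposed to improve consent and adherence, which the described models do not examine.

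**Working it through.** **1. The plan's only figure.** It states 80% power with 120 patients for an odds ratio of 3 at level 0.05, with a variance inflation factor of 1.2. The effective sample is 120 / 1.2 = 100. With a factor present in half the patients and an even preference split (both assumed, as the article gives neither) and a two-sided test:

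power = Φ(√(100 × 0.5 × 0.5 × 0.5 × 0.5) × ln 3 − 1.96) = Φ(2.5 × 1.0986 − 1.96) = Φ(0.787) ≈ 78%.

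The stated 80% is roughly reproduced under these favourable assumptions. It concerns preference only and says nothing about refusal, drop-out or cross-over.

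**2. Aim against described measure and analysis.**

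| Quantity in the aims | Described measure | Described pilot analysis |
|---|---|---|
| Consent / refusal | Interviews, n = 10–15 | None named |
| Acceptance of randomization | Interviews, n = 10–15 | None named |
| Compliance / cross-over | Interviews, n = 10–15; closing question on one group | None named |
| Drop-out | None | None |
| Arm preference | PDAQ, n = 120 | Logistic regression |
| Histology, neoadjuvant type, pCR | Treatment data, n = 120 | Descriptive |

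**3. What the design can yield.** There is one measurement per patient and no follow-up, and participants do not enter the RCT. Refusal and change of arm can be asked about hypothetically, but the answers cannot be linked to later behaviour. Some respondents will already have had surgery, so for them the question is more hypothetical still. Drop-out happens over time within a trial, and nothing in the design measures it.

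**4. Precision if the questions were asked.** The article gives no expected acceptance share, so 70% is assumed.

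- All 120 patients: half-width = 1.96 × √(0.7 × 0.3 / 120) = 1.96 × 0.0418 = 0.082, about ±8 points. The Wilson 95% interval for 84/120 is 61% to 77%.
- By preferred arm, assuming 60 patients in each: 1.96 × √(0.7 × 0.3 / 60) = 0.116, about ±12 points.
- Other assumed shares at n = 120: ±5.4 points at 10%, ±7.2 at 20%, ±8.9 at 50%.
- Interviews alone: Wilson 95% interval 40% to 89% for 7/10, and 42% to 85% for 10/15 (a share of 67%, so not an exact match to 70%).

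The interviews are planned as qualitative work, so the last line shows only that they could not take the survey's place as a source of rates.

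**The case against.** A reader might infer that the article promises observed rates, that its statistical section withdraws the aim, and that the planners will receive none of the three. The text does not support this. The aims speak of information on likelihood and of an intention to refine estimates. The biostatistics section says the pilot mainly has two objectives, places the regression alongside descriptive analyses, and repeats consent and adherence in objective 1. The PDAQ is not yet written and will grow out of interviews that ask about willingness and group change, so suitable items may well be intended. Item content is also something a condensed article can leave to the full protocol, and the flow chart of pilot procedures is not shown. Exclusion from the RCT does not stop anyone asking about intentions.

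A reader might also infer that the preference item has no neutral option. The article gives a two-way regression contrast, not the response format, so that remains unknown.

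These points remove the absolute claim for refusal and cross-over, where stated intentions could be tabulated. They do not supply the missing link. The article itself names its modelled outcome and its list of RCT assumptions, and neither matches the stated aim. For drop-out, no item in a one-time survey would help.

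**Conclusion.** The mismatch is real and of moderate severity. As described, the pilot analysis does not serve the aim of refining refusal and cross-over estimates. At best the design can supply stated intentions for those two, and it cannot supply a drop-out rate. No planned estimate is biased, and the development of the information material can proceed.

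The gain from acting is a stated-acceptance proportion known to about ±8 points at n = 120, in place of no described pilot estimate. That figure rests on the assumed 70% share and on complete answers from all 120 patients. It measures sampling error only and does not cover the gap between what patients say and what they would do.

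**What to change.** Before the PDAQ is final:

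- Make sure it asks all 120 patients whether they would join the RCT, whether they would accept randomization, and, for each arm separately, whether they would accept the allocation or leave it.
- In the Pilot Phase part of Biostatistical Planning and Analysis, add these as descriptive proportions with 95% confidence intervals, overall and by preferred arm. Analyse acceptance of randomization as an outcome beside preference, with p-values read descriptively as already planned.
- In Aims and Purpose of the Study, replace the refusal and cross-over rates with stated intention to refuse or to change arm, and remove the drop-out claim.
- Optionally, offer a no-preference answer in the preference item.

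The cost is a few items, one more descriptive analysis and reworded aims, with no extra patients. The drawback is that stated intentions are weaker evidence than observed behaviour; they must be labelled as such wherever they feed RCT planning.
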